#### Intervention effectiveness analyses

To investigate the effectiveness of Featback with and without weekly expert-patient support, within-group and between-group effect sizes (Cohen’s *d*) will be calculated (i.e., the effects of time and intervention) using the pooled standard deviation of each group. We are mainly interested in the effect from baseline to post-intervention (T0–T1), but to see if effects are maintained over the short and long term, analyses will be repeated for T1–T3 and T1–T5 respectively.
 To answer the first and main hypothesis that the active interventions (i.e., Featback, expert-patient support, and Featback plus expert-patient support) are more effective than a waiting list in reducing ED symptomatology (i.e., primary outcome EDE-Q global score), the three active intervention conditions will be compared to the waiting list condition. Repeated measures ANOVA will be used for T0–T1 to test this hypothesis. To see if the effects are maintained, these analyses are repeated for T1–T3 and T1–T5. The second hypothesis was that the combination of Featback and expert-patient support would be more effective than Featback or expert-patient support alone. A repeated measures ANOVA with post hoc tests will be conducted to compare T0–T1 differences in ED symptomatology between the four conditions. The post hoc analyses apply the Bonferroni correction for multiple testing. To see if these effects are maintained, these analyses are repeated for T1–T3 and T1–T5.

These confirmatory analyses will be repeated controlling for significant baseline variables (i.e., age, duration of ED psychopathology, number of psychological healthcare appointments). Additionally, the main analyses will be repeated for completers only.

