### Sample size calculation

An a priori statistical power analysis was conducted in G*Power version 3.1 to determine the optimal sample size having 80% power to detect a small effect size (*f* = 0.15, which corresponds to *d* = 0.30) between the active intervention conditions on the one hand and the control condition on the other. Consequently, the sample size calculation was based on a between-factors repeated measures analysis of variance (ANOVA) with two groups and two measurements (i.e., baseline and post-intervention; T0–T1). A significance level of α = 0.05 was maintained. The effect size was based on data from a previous RCT [20]. Calculations indicated a total of 264 participants will be needed, meaning 88 participants per condition. We assume a Pearson correlation of 0.5 between the outcome variable on baseline and post-intervention (i.e., T0–T1), which explains 25% of the variance of the outcome variable. Therefore, the sample size per group can be reduced by 25%. However, adjusting for an anticipated dropout rate between T0 and T1 of 25% (based on previous data), we will still need 88 participants per condition (*N* = 352). The high dropout rate introduces a risk of bias through selective dropout. However, participants in the previous Featback trial [20] who dropped out during the intervention did not differ from those who did not drop out with regard to ED psychopathology, ED quality of life, comorbid anxiety or depression, age, weight, hours spent online, allocated condition, and duration of their eating problems. Hence, bias because of selective dropout in the current sample is, at least based on these variables, improbable.

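### The primary T0–T1 repeated measures ANOVA is a change-score test, which is less efficient than the baseline-adjusted analysis whose 25% saving the sample size takes

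*Protocol article*

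**What the plan says.** Under Intervention effectiveness analyses, the first hypothesis compares the three active conditions with the waiting list on the EDE-Q global score: "Repeated measures ANOVA will be used for T0–T1 to test this hypothesis". The second hypothesis uses the same kind of test: "A repeated measures ANOVA with post hoc tests will be conducted to compare T0–T1 differences in ED symptomatology between the four conditions". An adjusted repeat is planned: "These confirmatory analyses will be repeated controlling for significant baseline variables (i.e., age, duration of ED psychopathology, number of psychological healthcare appointments"). That list is closed by its "i.e." wording and does not contain baseline EDE-Q.

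Under Sample size calculation, the aim is "to determine the optimal sample size having 80% power to detect a small effect size" (f = 0.15, equated to d = 0.30), with the calculation "based on a between-factors repeated measures analysis of variance (ANOVA) with two groups and two measurements" and α = 0.05. The result is 264 in total, given as 88 per condition. The section then assumes a T0–T1 correlation of 0.5, "which explains 25% of the variance of the outcome variable", and reduces each group by 25%. Anticipated dropout of 25% brings the number back to 88 per condition, 352 in all.

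Under Statistical analyses, all randomised participants are included and missing data are multiply imputed.

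**The concern.** The sample size section and the analysis section use the baseline score in different ways. The 25% is the square of the correlation, which is the variance removed when T1 is regressed on T0. The named test instead subtracts T0 from T1. At a correlation of 0.5, subtraction adds as much noise as it removes. The design therefore takes credit for a gain that its primary test is not built to deliver, and that credit is what offsets the dropout allowance. At stake is precision on the primary endpoint, from a covariate that every randomised participant has already supplied.

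**Working it through.** **Inputs.** From Sample size calculation: f = 0.15 (d = 0.30), α = 0.05, power 80%, two measurements, r = 0.5, dropout 25%, 88 per condition. Two-tailed testing is from Statistical analyses. The comparison of three active conditions with one control, from Intervention effectiveness analyses, gives 264 v 88 randomised, a 3:1 ratio. My assumptions: d = 0.30 is the standardised difference at T1, and the SD is the same at T0 and T1.

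**Step 1: reproduce the plan's figures.** For the between-factors repeated measures ANOVA, the noncentrality is λ = f²·N·m/(1 + (m − 1)r). With N = 264, m = 2 and r = 0.5, λ = 0.0225 × 264 × 2/1.5 = 7.92 on 1 and 262 df, giving power 0.80. So 264 reproduces. The last step also reproduces: 88 × 0.75 = 66, and 66/0.75 = 88 per condition, or 352.

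**Step 2: variance per participant for each analysis.**
- Change score (group-by-time test with two time points): 2(1 − r) = 2 × 0.5 = 1.00 SD².
- T1 adjusted for T0: 1 − r² = 1 − 0.25 = 0.75 SD².
- Ratio, adjusted to change: (1 − r²)/(2(1 − r)) = (1 + r)/2 = 0.75 at r = 0.5. It is below 1 for every r below 1.

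**Step 3: power on completers.** After 25% dropout there are 66 v 198, and 1/66 + 1/198 = 0.0202.
- Change: SE = √(1.00 × 0.0202) = 0.142, and 0.30/0.142 = 2.11. Power is 0.56.
- Adjusted: SE = √(0.75 × 0.0202) = 0.123, and 0.30/0.123 = 2.44. Power is 0.68.

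**Step 4: power under the planned imputation.** T0 is completed before randomisation, so it is known for everyone. Imputing T1 from T0 gives the change score a per-arm variance of (1 − r²)/n_obs + (1 − r)²/n_all, in the limit of many imputations.
- Waiting list: 0.75/66 + 0.25/88 = 0.01420.
- Active: 0.75/198 + 0.25/264 = 0.00473.
- The sum is 0.01894, so SE = 0.138 and 0.30/0.138 = 2.18. Power is 0.58 (noncentral t) to 0.59 (normal approximation).
- The adjusted analysis keeps variance 0.01515 and power 0.68. The variance ratio is 0.01515/0.01894 = 0.80.

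**Step 5: dependence on r (completers, 66 v 198, d = 0.30).**

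| r | Variance ratio | Power, change | Power, adjusted |
|---|---|---|---|
| 0.3 | 0.65 | 0.43 | 0.60 |
| 0.5 | 0.75 | 0.56 | 0.68 |
| 0.7 | 0.85 | 0.77 | 0.84 |
| 0.8 | 0.90 | 0.91 | 0.94 |

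**Step 6: why adjustment alone does not reach 80%.** The 264 already uses r = 0.5 through the factor (1 + r)/2 = 0.75: without repeated measures the same f needs 352, and 352 × 0.75 = 264. The further 25% cut uses the correlation a second time. Also, 264 is a total for two groups (132 each), but it was spread as 88 over three conditions. At 3:1 and r = 0.5, the adjusted analysis needs 88 waiting-list completers for 80% power, and the change score needs 117. The plan expects 66.

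**The case against.** Four objections have force.

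**The planned test is not an error.** With randomised groups, the change-score test has the correct type I error and no bias averaged over randomisations. A reader might infer from the missing baseline adjustment that the estimate is biased by chance imbalance in EDE-Q. It is not. Such imbalance appears as extra variance, which the power figures already count.

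**Imputation recovers part of the gain.** A reader might say that the planned analysis obtains none of the credited saving. That is true of a completers-only change score at r = 0.5. The protocol imputes T1 for all randomised participants, however, so some of the information in T0 returns. The variance ratio is then 0.80 and not 0.75, and the power gap is about 0.10 and not 0.12. It shrinks but remains.

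**The size depends on r.** At r = 0.8 the completer gap is 0.03. The value 0.5 is the protocol's own assumption, so it is the fair reference point, but a gain equivalent to one third more participants (1/0.75 = 1.33) applies only there and only to completers.

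**The tested term is probably group-by-time.** Because the sample size names a between-factors ANOVA, a reader might infer that the primary test is the group main effect averaged over T0 and T1, with much lower power still. The analysis section does not support that. It states its interest as the effect from baseline to post-intervention and, for the second hypothesis, compares T0–T1 differences. The between-factors label appears only in the sample size description.

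**Conclusion.** The point holds as a matter of efficiency and of consistency between two sections. The sample size takes a 25% reduction that belongs to a baseline-adjusted analysis, while the primary test is a change-score test and no effectiveness analysis adjusts for baseline EDE-Q. At the protocol's r = 0.5, d = 0.30 and 25% dropout, the cost is roughly 10 percentage points of power under multiple imputation (0.58–0.59 v 0.68) and 12 on completers (0.56 v 0.68). The direction holds for any r below 1 under a common SD. The size rests on r, on d being the T1 difference, and on imputing T1 from T0.

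A reader might also infer that switching to baseline adjustment would make good the stated 80%. It would not: power is 0.68 at the planned numbers, because of the separate faults in the sample size shown in Step 6.

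**What to change.** Make the primary analysis of the first hypothesis, and the T0–T1 part of the second, a linear regression (ANCOVA) of T1 EDE-Q global on the arm contrast and T0 EDE-Q global. Fit it in each imputed dataset, pool the results, name the tested coefficient, and report the adjusted difference with its 95% confidence interval. Leave T1–T3 and T1–T5 as they are: they ask whether effects are maintained after T1, and a follow-up score adjusted for T0 would answer a different question.

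Restate the power in Sample size calculation for the chosen test at 3:1 allocation, using the correlation once. At r = 0.5 and 25% dropout, 80% power needs 118 per condition (88/0.75, N = 472) with baseline adjustment, or 156 (117/0.75, N = 624) with the change score. If 352 is kept, state the power it gives.

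The analysis change costs wording only, since T0 EDE-Q is already collected and the software is unchanged. The power restatement costs a short recalculation, and participants only if the sponsor decides to enlarge the trial.

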### Aims and research questions

The current study builds on the study by Aardoom et al. [20] by investigating whether the results regarding the effectiveness of Featback will hold. More specifically, the first aim is to investigate the (cost-)effectiveness of the Internet-based intervention Featback in comparison to Featback with support from an expert patient, support from an expert patient without Featback, and a waiting list control condition (WLC). The primary outcome measures of the current study are ED-related attitudes. Secondary outcome measures include self-efficacy, social support, symptoms of depression and anxiety, motivation to change, user satisfaction, intervention usage, and help-seeking attitudes and behaviors. Finally, cost-effectiveness will be evaluated through the reported quality of life, outcomes for patients in terms of capabilities, and medical and societal costs. We have two hypotheses accompanying the first research aim.
 Our primary hypothesis is that Featback without expert-patient support, Featback with expert-patient support, and expert-patient support without Featback will be more effective in reducing ED psychopathology and more cost-effective compared to a waiting list. Secondly, we hypothesize that the combination of expert-patient support plus an online intervention will be more effective in reducing ED psychopathology and more cost-effective compared to expert-patient support or Featback only and that the improved effectiveness will be maintained up until a year later.

The second aim of this study is to investigate predictors and moderators of intervention response to explore what works for whom. Predictors and moderators that will be tested as predictors or moderators of treatment response and/or intervention usage are age, gender, and educational level, motivation to change, social support, severity of ED symptoms, severity of symptoms of depression and anxiety, self-efficacy, self-esteem, and closeness or perceived similarity of participants with expert patients. Additionally, self-efficacy is examined as a mediator. Besides the exploratory tests, there are two hypotheses concerning the second aim of this study.

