## Methods

### Design

Since the present study is a continuation of previous work of this research group, the methodology described here will be similar and in some parts identical to the previous design [19]. The current study describes an RCT with a two-by-two factorial design with repeated measures to create four different conditions: (1) Featback, comprising psychoeducation and a fully automated self-monitoring and feedback system, (2) Featback with weekly individualized support by an expert patient through e-mail or chat, (3) weekly individualized support by an expert patient through e-mail or chat, and (4) a waiting list. A description of the content of the interventions for each condition is presented below. After screening, all eligible participants are asked to give informed consent and fill in online baseline measures (T0). Subsequently, they will be randomized to one of the four conditions. An independent researcher will conduct randomized allocation by using the SPSS function to produce random numbers. Hence, the main researcher will be blind to the randomization process. Randomization will take place in blocks of 40 participants. The current design does not allow expert patients to be blinded to the study goal, since they are required to help participants with their ED or ED-related problems to the best of their abilities within the intervention protocol. Naturally, expert patients know that the individuals they have contact with via e-mail or chat are randomized to one of the expert-patient support conditions. Similarly, participants are not blinded concerning the condition allocation.

After 8 weeks (intervention period or waiting period), participants are invited to complete the post-intervention assessment (T1). Finally, a link to the online follow-up questionnaires will be sent to them 3 (T2), 6 (T3), 9 (T4), and 12 (T5) months after T1 (see Fig. 1). Ethical approval has been obtained by an independent medical ethics committee (CME LUMC Leiden, file number NL64553.058.18). The Standard Protocol Items: Recommendations for Interventional Trials (SPIRIT) checklist is provided as Additional file 1.

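### Maintenance is assessed by ANOVAs on T1–T3 and T1–T5, and no between-arm EDE-Q effect at T3 or T5 relative to the pre-randomisation baseline is specified, so H2's one-year claim cannot be supported

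*Protocol article*

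**What the plan says.** All of the following is in the protocol article.

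- **Hypothesis.** Under Aims and research questions, H2 states that the combination beats either component alone and "that the improved effectiveness will be maintained up until a year later".
- **Visits.** The Design section places follow-up at "3 (T2), 6 (T3), 9 (T4), and 12 (T5) months after T1". The waiting list lasts 14 months (Waiting list control), so a randomised control group is still in place at T5.
- **H1 analysis** (Intervention effectiveness analyses). The three active arms are compared with the waiting list on EDE-Q global score: "Repeated measures ANOVA will be used for T0–T1 to test this hypothesis". Then: "To see if the effects are maintained, these analyses are repeated for" T1–T3 and T1–T5.
- **H2 analysis** (same section). A four-arm repeated measures ANOVA with Bonferroni post hoc tests compares T0–T1 differences. Then: "To see if these effects are maintained, these analyses are repeated for T1–T3 and T1–T5".
- **Effect sizes** (same section). Within-group and between-group Cohen's *d* follow the same windows: "to see if effects are maintained over the short and long term, analyses will be repeated for T1–T3 and T1–T5 respectively".

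The article gives no T0–T3 or T0–T5 analysis of EDE-Q between arms, no baseline-adjusted comparison at T3 or T5, and no margin or criterion for calling an effect maintained.

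**The concern.** To show that an effect is still present at a year, one needs the between-arm difference at a year, judged against the pre-randomisation baseline. Replacing T0 by T1 as the starting point removes that quantity. T1 is measured after treatment, so the benefit to be followed is already in the reference value.

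The method is stated three times with its purpose attached, so this is not a detail left for the SAP. At stake are H2's one-year clause and any long-term reading of H1. An effect that has faded could be described as maintained, and one that has persisted would have no estimate to demonstrate it.

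**Working it through.** **What each ANOVA term tests when anchored at T1.** Let d1 and d5 be the active-minus-control differences at T1 and T5, in SD units.

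- Group-by-time tests d5 − d1 = 0. Full maintenance (d5 = d1) is the null. So is the case where there was never an effect (both zero).
- The group main effect tests (d1 + d5)/2 = 0. It can be non-zero through d1 alone.
- Neither term tests d5.

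H2's wording, which compares differences over a window between conditions, points to group-by-time. The H1 term is not named.

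**Inputs** (Sample size calculation): d = 0.30 (f = 0.15), two-sided alpha 0.05, T0–T1 correlation 0.5, 25% dropout, 88 per condition. After dropout 88 × 0.75 = 66 per arm, so 3 × 66 = 198 active v 66 waiting list. The correlation for T1–T5 is not given; I assume 0.5 and vary it to 0.7.

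**The plan's own figure.** For the between-factors ANOVA, lambda = 0.15² × 264 × 2 / (1 + 0.5) = 7.92, giving power 0.801. The stated 264 reproduces and is not in dispute here.

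**Group-by-time test on T1–T5.** SD of change = √(2(1 − r)) = 1 at r = 0.5. SE = √(1/198 + 1/66) = 0.142.

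| True course | Loss/SE | Power | Loss missed |
|---|---|---|---|
| 0.30 at T1, 0 at T5 | 0.30/0.142 = 2.11 | 0.56 | 44% |
| 0.30 at T1, 0.15 at T5 | 0.15/0.142 = 1.06 | 0.18 | 82% |

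At r = 0.7 the SD of change is √0.6 = 0.775 and the SE is 0.110; complete loss is then missed 22% to 23% of the time. With all 352 analysed at r = 0.5, the figures for complete and half loss are 32% and 77%.

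**Requiring a T1 benefit first.** With equal correlations of 0.5 between visits, the T0–T1 and T1–T5 change estimates correlate −0.5. For complete loss, the z-statistics have means 2.11 and 2.11 in opposite directions. From the bivariate normal, a significant T1 benefit followed by a non-significant T1–T5 test has probability 0.165. A significant T1 benefit alone has probability 0.56. So 0.165/0.56 ≈ 0.29: about 30% of trials with a T1 effect, or about 16% of all trials.

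**Group main effect on T1 and T5.** SD of the two-visit mean = √((1 + 0.5)/2) = 0.866; SE = 0.866 × 0.142 = 0.123.

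- Maintained: 0.30/0.123 = 2.44, rejection probability 0.68.
- Wholly lost: 0.15/0.123 = 1.22, rejection probability 0.23.
- Never any effect: 0.05.

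So after complete loss this term is still significant 23% of the time, through the T1 difference.

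**T0-adjusted difference at T5.** Residual SD = √(1 − 0.5²) = 0.866, taking the T0–T5 correlation also as 0.5. At 198 v 66 the SE is 0.123, power for d = 0.30 is 0.68 and the 95% CI half-width is 0.24 SD. With all 352, power is 0.80 and the half-width 0.21.

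**The case against.** Several points on the other side stand.

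- A reader might infer that the plan treats a non-significant T1–T5 result as proof of maintenance. It does not say so. It states a purpose and no criterion, and a criterion may sit in an SAP that is not shown.
- The H1 term is not named, and the sample size was computed for the between-groups effect. With that term, a maintained effect would tend to appear as a significant result. The null-hypothesis argument is therefore firm for H2's wording and conditional for H1.
- It would be too strong to say that nothing randomised is compared after T1. Differences in T1–T5 change, and the average of two visits, both compare randomised arms. What is missing is the narrower quantity, the effect at T3 or T5 relative to T0.
- The 44% is the miss rate of one test, not the share of trials that would wrongly report maintenance, because that claim presupposes a T0–T1 effect. If there was never an effect, a significant T1 benefit followed by a non-significant T1–T5 test occurs only about 2% of the time.
- A figure for H2's pairwise tests would need an effect size between active arms and a number of Bonferroni comparisons. The article gives neither, so none is offered.
- The article says that interest lies mainly in T0–T1, and the one-year clause belongs to H2.

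None of this supplies the missing comparison. H3 uses gains to T5, but only in relation to perceived similarity with the expert patient. The QALY area under the curve concerns utilities.

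**Conclusion.** The point holds in a limited form. The stated maintenance analyses cannot answer H2's one-year claim under either reading of the ANOVA term, because neither estimates the between-arm EDE-Q effect at T3 or T5 against baseline.

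For the active-versus-waiting-list contrast, complete loss of d = 0.30 would be missed 44% of the time by the group-by-time test, about 30% given a significant T1 benefit. Loss of half the effect would be missed 82% of the time. These figures assume 198 v 66 at T5, which takes the T0–T1 dropout as final, and r = 0.5 for T1–T5. At r = 0.7 the 44% halves to 22–23%. The structural defect does not depend on these numbers.

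The documents do not support extending this to the primary T0–T1 test, which is unaffected.

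**What to change.** For H1 and H2, replace or supplement the T1–T3 and T1–T5 tests with T0-adjusted between-arm differences in EDE-Q global score at T3 and at T5, with 95% CIs. ANCOVA on T0 or one longitudinal model over T1–T5 would serve. Adding T0–T3 and T0–T5 to the existing ANOVA is the minimum, at lower power: for d = 0.30 at 198 v 66, 0.56 against 0.68 for ANCOVA.

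State that a maintenance claim requires the CI for that difference to exclude zero in favour of the intervention. For H2 this means the combination against each single component. Report T1-to-T3 and T1-to-T5 change descriptively, with CIs.

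The cost is revised wording and a little more analysis; the assessments are already scheduled. The downside is modest power at T5: about 0.68 for a persisting d = 0.30 at 198 v 66, and 0.23 if only half the effect remains. An inconclusive interval should then be reported as inconclusive.

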### Statistical analyses

All statistical analyses will be conducted in SPSS version 25 and the R statistical programming environment [85]. A two-tailed significance level of *α* = .05 will be maintained throughout the analyses unless indicated otherwise. All analyses will be conducted according to the intention-to-treat (ITT) approach. This means that all participants who underwent randomization, even those who withdrew from the study or deviated from the protocol, are included in the analyses. For the effectiveness analyses, both ITT and completers analyses will be conducted. A participant is considered a completer when he/she has completed at least five monitoring assessments (i.e., Featback only condition), five support sessions (i.e., expert-patient support only condition), or both (i.e., Featback plus expert-patient support condition).

Missing data will be handled using multiple imputation [86]. Multiple imputations using predictive mean matching will be conducted in the statistical programming environment R [85]. Interactions will be taken into account in the imputation procedure [87]. Multiple imputation methods have several advantages over complete-case analyses or single imputation techniques and are therefore highly recommended [86, 88].

Homogeneity of groups (i.e., between-group differences) will be assessed at baseline (T0) using chi-square tests for categorical variables and ANOVAs for continuous variables. Additionally, homogeneity of variances will be assessed using Levene’s statistic, and non-parametric testing will be used when appropriate.

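### H2 names two contrasts, but it is tested by Bonferroni post hoc comparisons in a four-condition ANOVA with no stated family and no use of the factorial layout; power is well below 80% on every reading

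*Protocol article*

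**What the plan says.** Under Design, the protocol describes "an RCT with a two-by-two factorial design with repeated measures". Under Aims and research questions, H2 states that the combination "will be more effective in reducing ED psychopathology and more cost-effective compared to expert-patient support or Featback only". The Intervention effectiveness analyses section repeats this as "The second hypothesis was that the combination of Featback and expert-patient support would be more effective than Featback or expert-patient support alone".

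The same section gives the test: "A repeated measures ANOVA with post hoc tests will be conducted to compare" the change in symptoms from T0 to T1 across all four conditions. It then adds: "The post hoc analyses apply the Bonferroni correction for multiple testing". The number of comparisons in that correction is not given. The general level is two-sided 0.05.

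The section has no test of the Featback factor, the support factor or their interaction. H1 compares the three active conditions with the waiting list. The Sample size calculation covers only active conditions against control; no contrast between active conditions is powered.

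**The concern.** H2 is specified in advance, names its two contrasts and is listed among the confirmatory analyses. Generic post hoc testing does not match it. Four conditions make six pairs, and correcting for all six lowers the per-comparison level from 0.05 to 0.0083 for a hypothesis that asks about two of them. The added value of expert-patient support is in the trial's title, yet the factorial layout that bears on it is not used in any effectiveness analysis.

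The risk lies in interpretation. A non-significant H2 would be the likely result even if support truly added d = 0.30. It could then be read as evidence that support adds nothing, which is how the earlier therapist-support trial is summarised in the Background.

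**Working it through.** **Inputs (Sample size calculation).** f = 0.15, equivalent to d = 0.30; T0–T1 correlation r = 0.5; 88 randomised per condition; 25% dropout by T1; two-sided α = 0.05.

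**The plan's own figure.** For a between-factors repeated measures ANOVA with two groups and two measurements, λ = N·f²·m / (1 + (m − 1)r). At N = 264, λ = 264 × 0.0225 × 2 / 1.5 = 7.92, which gives power 0.801. The stated 264 is reproduced, but it concerns active against control. The 88 per condition is taken as given here.

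**Sample per arm for H2.** 88 × 0.75 = 66 with T1 data. The plan uses multiple imputation under intention to treat, so 66 (imputed cases add no information) and 88 (no information is lost) bracket the effective size.

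**Standard deviation, in units of the raw SD.** The group-by-time test at two time points is a test of change scores: SD = √(2(1 − r)) = √1 = 1. With ANCOVA on baseline: SD = √(1 − r²) = √0.75 = 0.866.

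**Level.** Six pairs: 0.05/6 = 0.0083. Two contrasts: 0.05/2 = 0.025.

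**Power per contrast.** Two-sample noncentral t with noncentrality (d/SD)·√(n/2). For 66 per arm on change this is 0.30 × √33 = 1.72, against a critical value of 2.68 at level 0.0083; power is 0.174.

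| n per arm, model | 0.05/6 | 0.05/2 | 0.05 | d = 0.15, 0.05/6 |
|---|---|---|---|---|
| 66, change | 0.17 | 0.30 | 0.40 | 0.04 |
| 66, ANCOVA | 0.25 | 0.39 | 0.51 | 0.05 |
| 88, change | 0.25 | 0.40 | 0.51 | 0.05 |
| 88, ANCOVA | 0.36 | 0.52 | 0.63 | 0.07 |

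All columns but the last use d = 0.30. The planned repeated measures ANOVA corresponds to the change rows.

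**Both contrasts (simulation with the shared combination arm, 66 per arm, d = 0.30).** Six-pair correction on change: about 0.07. Each at 0.05 with ANCOVA: about 0.34.

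**Size needed for 80% per contrast on change.** About 270 per arm with data (six pairs) or 212 (two contrasts).

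**Factorial main effect of support.** 2 × 66 = 132 against 132 at two-sided 0.05, d = 0.30: 0.68 on change, 0.80 with ANCOVA. This assumes the same effect with and without Featback. If support adds nothing to Featback but beats the waiting list by 0.30, the main effect is (0 + 0.30)/2 = 0.15. It would then be significant with probability 0.23 (change) or 0.29 (ANCOVA) although H2 is false.

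**The case against.** - **H2 is not the primary hypothesis.** H1 is, and only H1 was powered. The Design section presents the factorial as a way to form four conditions, and analysing such a trial as four arms is a recognised choice when an interaction is possible. Bonferroni is conservative but valid. All of this stands, so the plan is inefficient and unclear for H2 rather than invalid.
- **A reader might infer that power is 17%.** That is the lowest of several readings. The family of six is inferred from the comparison of four conditions, 66 per arm gives imputed cases no weight, and d = 0.30 was chosen for a different comparison. The last point cuts the other way: the Background reports no difference between active interventions in the earlier trial.
- **A reader might infer that four of the six comparisons are wasted.** H1 as worded in the aims concerns each active condition against the waiting list. Three of those four pairs therefore bear on a stated hypothesis, although H1 has its own analysis.
- **A reader might infer that no correction is needed.** That holds only if H2 requires superiority over both components. The wording joins the two components with *or*. If either contrast may be claimed alone, a correction over two is legitimate.
- **A reader might infer that the main effect of support, at 0.80, answers H2.** It averages combination against Featback with support against waiting list. The example in the working shows that it can be significant when H2 is false.

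**Conclusion.** The point holds in this form. H2's two contrasts are tested through a post hoc procedure whose family is undefined, and the declared factorial structure is not used in any effectiveness analysis. At d = 0.30 and r = 0.5, power per contrast is 0.17 to 0.36 with six pairs, which is the natural reading of the text, and 0.30 to 0.52 with two. At d = 0.15 the six-pair figure is 0.04 to 0.07. These values rest on carrying d = 0.30 over from the comparison with the waiting list.

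The documents do not support a single power figure, nor the view that a better analysis makes H2 adequately powered. Under the proposed contrasts, power at 66 per arm reaches 0.51 each and about 0.34 for both. H1 is not affected. The change is worth making because it costs almost nothing and uses a baseline measure already collected.

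**What to change.** 1. Replace the post hoc tests for H2 by two planned contrasts, combination against Featback and combination against support, from a model of T1 EDE-Q adjusted for baseline EDE-Q (ANCOVA).
2. State what H2 requires. If both contrasts, test each at two-sided 0.05 and claim H2 only if both favour the combination. If either may be claimed alone, correct over these two only (0.025 each; power 0.39 at 66 per arm).
3. Add a pre-specified supportive factorial ANCOVA with Featback, support, Featback × support and baseline EDE-Q. Report the interaction with its confidence interval and the simple effects. Read the main effect of support as added value only under additivity, and not in place of the H2 contrasts.
4. State the power for H2 as a range, with its assumptions, and say that it is below 80%.

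Cost: wording in the analysis section, fixed before analysis. No extra participants, visits or measures are needed. The downsides are that H2 remains underpowered and that the factorial main effect is an average over the other factor.
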